### Patient flow

We will use a CONSORT 2010 flow diagram to present the participant flow [22]. This diagram will report how many infants were screened, eligible for the trial and excluded due to our exclusion criteria. We will record the age and sex for all screened patients and provide descriptive statistics for these quantities. The CONSORT diagram will also detail the number of participants who are lost to follow-up and who discontinue the intervention. Finally, we will also highlight the number of participants who were randomised but excluded from the primary analysis. Participants will be free to withdraw from the BIPED study at any time, and an investigator can discontinue or withdraw a patient if it would not be in the best interest of the participant to continue. The reason for, and the number of, study withdrawals will be tabulated for each treatment option.

### Protocol deviations

We define protocol deviations as participants who are randomised to either treatment but do not receive all of the study medications in the ED and participants who receive their ED medications at the incorrect dose and time, allowing for 5% tolerance on dose. Treatment adherence is taking all the trial medications. Adherence will be monitored by research staff in the ED, and the additional dose of dexamethasone will be assessed through questions on the day seven follow-up survey. We will report the proportion of patients who had full adherence by treatment group. The number (and percentage) of patients with protocol deviations will be summarised by treatment group. The number of patients included in the intention-to-treat analysis will be used to calculate the percentage of participants with a protocol deviation. We will not undertake inferential statistical analysis for protocol deviations.

### Analysis populations

The primary analysis will include all randomised participants for whom outcome data are available and who do not withdraw consent for the use of their data as an intention-to-treat analysis. A per protocol analysis that includes only eligible participants for whom we have outcome data, who do not withdraw consent for the use of their data, who complete all their ED-based medications and receive the correct dose (within ± 5%) and timing of medications will also be performed. Finally, we will examine our outcomes in the per protocol population while also excluding participants who did not take their second dose of oral medication (unless admitted to hospital within the 40-h second dose of oral medication window).

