## Method/Design

### Design and setting

The BIPED study is a phase III study conducted in 12 sites across Canada, Australia and New Zealand. All participating hospitals are members of the Pediatric Emergency Research Canada (PERC) network [11] or the Paediatric Research in Emergency Departments International Collaboration (PREDICT) [12], both of which are affiliated with the Pediatric Emergency Research Networks (PERN). The BIPED study will define bronchiolitis as an episode of wheezing or crackles in an infant aged between 60 days and 12 months, alongside signs of an upper respiratory tract infection during the period deemed to be the season for RSV bronchiolitis. To reflect international clinical guidelines and practice, we have not restricted our definition of bronchiolitis to the first episode of wheezing or crackles and will enrol infants with second and subsequent episodes of bronchiolitis, with each infant only enrolled once into the study.

The active treatment in the BIPED study is two treatments of epinephrine (either via nebulisation (3 mg) or via metered dose inhaler and spacer (MDI-s) (625 mcg)) given 30 min apart in the ED and two doses of once daily oral dexamethasone (0.6 mg/kg per dose, up to a maximum of 10 mg), known as EpiDex. The first dose of dexamethasone will be given immediately before the first dose of epinephrine, and the second dose will be given 24 h later. The BIPED study will compare EpiDex to a placebo control (oral dexamethasone vehicle and nebulised normal saline or an inert placebo by MDI-s) by randomising participants in a 1:1 ratio. All study personnel, bedside clinicians, and participants/caregivers are blinded to the study group assignment. Participants will be followed up for 21 days following their ED enrolment visit, with the primary outcome collected at 7 days (168 h) post enrolment.

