### Primary outcome

The primary outcome is admission to hospital for bronchiolitis within 7 days (168 h) of study enrolment. BIPED study defines hospitalisation as any of the following conditions:The participant is admitted to an inpatient ward.An ED length of stay of 12 h or greater.A combined ED and observation unit length of stay of 12 h or greater.

ED length of stay at enrollment visit is defined as the time between the administration of first study medication (or time of consent when no study medications are received) and discharge from the ED or observation unit. The length of stay for all return ED visits will be measured from time of triage or registration, whichever is sooner.

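### The per-protocol population that also requires the second oral dose selects on the primary outcome: infants admitted early stay regardless of that dose, all others stay only if they took it

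*SAP article*

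**What the plan says.** The section on analysis populations in the SAP article defines three sets.

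- The primary, intention-to-treat set: "The primary analysis will include all randomised participants for whom outcome data are available", less those who withdraw consent for use of their data.
- A per-protocol set of eligible infants "who complete all their ED-based medications and receive the correct dose (within ± 5%) and timing of medications will also be performed".
- A third set, which takes the per-protocol set "while also excluding participants who did not take their second dose of oral medication", with one exception: "unless admitted to hospital within the 40-h second dose of oral medication window".

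Three other statements bear on the third set. On the outcome: "The primary outcome is admission to hospital for bronchiolitis within 7 days (168 h) of study enrolment". On timing, the section on design and setting says of dexamethasone that "the second dose will be given 24 h later". On measurement, the section on protocol deviations says that "the additional dose of dexamethasone will be assessed through questions on the day seven follow-up survey". No adjustment for the selection, and no caution on interpretation, accompanies the third set.

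**The concern.** The event that exempts an infant from exclusion is, in almost every case, the outcome being analysed. Within the per-protocol set, infants who missed the second dose are handled in three ways:

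- admitted inside the window: kept, and counted as events;
- first admitted after the window: dropped;
- never admitted: dropped from the denominator.

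Membership therefore depends on whether and when the outcome occurred. The arm risks from this set do not estimate the risk under full adherence. If second-dose adherence differs between arms, part of that difference appears as a treatment effect.

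**Working it through.** **Inputs from the SAP article.** Hospitalisation risk 0.35 and target difference 8 points (statistical principles), hence 0.35 against 0.27. The outcome window is 168 h and the second dose is due at 24 h. The article does not say when the 40-h window starts, but this does not matter here: counted from enrolment it ends at 40 h, and counted from the due time of the dose it ends at 24 + 40 = 64 h. Both lie inside 168 h.

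**Assumed inputs (not in the article).** Early admission risk E (inside the window) and late admission risk L: placebo 0.30 and 0.05, EpiDex 0.22 and 0.05. Proportion q missing the second dose among infants not admitted early: 0.10 or 0.20, unrelated to later admission. The article gives no figure that these results should reproduce.

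**Formula.** Kept events are E + L(1 − q). Kept infants are E + (1 − E)(1 − q). The risk read from the third set is the ratio of the two.

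**Equal adherence, q = 0.20 in both arms.**

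- Placebo: (0.30 + 0.05 × 0.8) / (0.30 + 0.70 × 0.8) = 0.34 / 0.86 = 39.5%, true value 35%.
- EpiDex: (0.22 + 0.05 × 0.8) / (0.22 + 0.78 × 0.8) = 0.26 / 0.844 = 30.8%, true value 27%.
- Contrast: −8.7 points against a true −8.0; relative risk 0.78 against 0.77.

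**No true effect (0.30 and 0.05 in both arms), unequal adherence.**

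- q = 0.20: 0.34 / 0.86 = 0.3953.
- q = 0.10: (0.30 + 0.045) / (0.30 + 0.63) = 0.345 / 0.93 = 0.3710.
- Difference: 2.4 points, relative risk 1.07 (arm with more missed doses against the other). It counts against EpiDex if EpiDex has the more missed doses, and in its favour if placebo does.

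**Range over the timing assumption.** Let the share of admissions falling inside the window be 0.70 to 1.00, the same in both arms, and keep the 20% against 10% pattern. The false difference under no effect runs from 2.0 to 2.8 points in either direction. A true −8.0 points reads −10.3 (share 0.70) to −11.1 (share 1.00) if placebo misses more doses, and −6.4 to −5.8 if EpiDex does.

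**Is inflation certain?** No. With E = 0.30, L = 0.05 and q = 0.10, suppose all late admissions occur in non-takers. The rule then gives 0.30 / 0.93 = 32.3%, below the true 35%.

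**Would deleting the exception repair it?** No. Take a true risk of 0.35, 85% of admissions inside the window and 10% missed among the others. If 30% of early-admitted infants lacked the second dose, the risk would read (0.35 × 0.85 × 0.7 + 0.35 × 0.15 × 0.9) / (the same + 0.65 × 0.9) = 0.2555 / 0.8405 = 0.304. If 50% lacked it, the risk would read 0.196 / 0.781 = 0.251.

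**Check of the remedy.** Keep all early admissions, then weight takers by 1/(1 − q). Placebo: 0.30 + 0.04/0.8 = 0.35. EpiDex: 0.22 + 0.04/0.8 = 0.27. Both true risks return, provided dose-taking is unrelated to later admission given the covariates in the weights.

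**The case against.** The exception has a sensible motive. An infant already admitted may have had no chance to take the dose, and dropping such infants would delete primary events. This stands: the fault lies in dropping non-takers who were not admitted early without any compensation, and not in keeping the early admissions.

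The trial is blinded to caregivers and clinicians, so a twofold difference in missed doses may not occur, and with equal adherence the contrast barely moves. This also stands, and it limits the size of the point. The article plans to report full adherence by group, so a difference would be visible, but seeing it does not correct the estimate.

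The exception speaks of hospital admission without restricting it to bronchiolitis, so the overlap with the primary outcome is near-complete by wording and not exact.

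A reader might infer that the first per-protocol set, restricted to infants "who complete all their ED-based medications and receive the correct dose", has the same defect because an infant could be admitted before completing the ED course. The article does not support this as a material problem. The first dexamethasone dose immediately precedes the first epinephrine treatment, and the second epinephrine treatment follows 30 min later. Two of the three hospitalisation criteria need a stay of at least 12 h, so only a ward admission within about half an hour could matter. Exempting admitted infants from that set would also create the very asymmetry described here.

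A reader might also infer that the trial's main conclusion is at risk. It is not: the primary analysis is by intention to treat and does not use this rule.

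**Conclusion.** The point holds: inclusion in the third population depends on the primary outcome. If missed doses are unrelated to later admission, both arm risks are inflated, by roughly 4 to 4.5 points under the assumed inputs with 20% missed. The contrast is little affected when adherence is equal (−8.7 against −8.0 points). It is biased by about 2.4 points under no effect when missed doses are 20% in one arm and 10% in the other (2.0 to 2.8 over the timing range). The admission timing and missed-dose rates are assumptions, and the direction of the bias depends on which arm misses more doses. If late admissions concentrate in non-takers, the risk can read low instead of high, so inflation should not be stated as certain. Priority is low to moderate, because this is a supportive analysis.

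**What to change.** Redefine the analysis of the third population as follows.

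- Keep every infant in the per-protocol set for admissions up to the end of the second-dose window, and state when that window starts.
- Among infants not yet admitted at that time, censor those who did not take the dose.
- Weight those who took it by the inverse probability of having done so, given arm, site and baseline covariates such as age, RDAI and oxygen saturation.
- Report the 168-h risk by arm, and tabulate by arm and admission status the infants whom the present rule would exclude.

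The cost is a change of SAP wording and a short weighted analysis on data already collected. It needs a model for adherence. It also assumes that nothing unmeasured after discharge, such as worsening symptoms, drives both dose-taking and later admission; that assumption should be stated with the result. Because second-dose adherence comes from the day-7 survey, the wording should also say how infants with no answer are handled.

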### Baseline characteristics

We will collect baseline information about the participants’ age, sex, weight, race, indigenous status and home environment, which includes the presence of smokers and attendance at daycare. We will also collect baseline clinical characteristics (respiratory distress assessment index (RDAI) [23], oxygen saturation, respiratory rate, heart rate, and temperature), the length of symptoms and treatments given prior to initial ED presentation, the medical history of the participant (such as breastfeeding, maternal smoking during pregnancy, prematurity, previous intubations, personal history of atopy [environmental allergy, food allergy and eczema, and previous significant/chronic illness], and previous episodes of wheezing/bronchiolitis) and family history of atopy (including asthma). Finally, if respiratory virus testing is available, the virus status will be reported.

Baseline characteristics will be compared across treatment groups and reported based on their data type. Specifically, categorical data will be summarised by numbers of participants within each category and percentages. If the continuous data are sufficiently normal, they will be summarised with the mean and standard deviation. Otherwise, the data will be summarised using the median and interquartile range. We will not undertake inferential statistics for baseline characteristics but will note the clinical importance of any imbalance.

### Analysis for the primary endpoint

We will compute the posterior probability that EpiDex results in a lower probability of hospitalisation than placebo using hierarchical Bayesian relative risk regression, adjusted for site. The prior for the treatment effect is from our expert elicitation exercise [17]. We will report the mean and 95% high-density posterior credible interval for the absolute risk difference and relative risk across the two treatment groups. A secondary analysis of the primary outcome will include only those participants who present with their first episode of bronchiolitis. All models will include minimally informative priors for the variance parameters [24] and other coefficients [25].

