### Randomisation and data collection

Eligible participants will be randomised using permuted-block randomisation, stratified by site. This randomisation strategy ensures that differences in standard practice across sites will be equally represented in each study group. Additionally, block randomisation ensures that seasonal variation in the response to therapy will be comparable across the two groups. The statistician performing providing the randomisation lists is not involved in the study in another capacity.

Study participant research data will be stored using the REDCap electronic data capture system [14], based at a secure data coordination centre (DCC) at the Women and Children’s Health Research Institute (WCHRI), University of Alberta [15]. Individual participants will be identified with a unique study identification number.

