## Statistical analysis plan

### Statistical principals

Outcomes will be collected with a standardised survey issued to parents/caregivers either over email or by telephone 7 and 21 days after enrollment in the BIPED study. Non-responders will be sent a second email and, if necessary, up to six attempted phone calls over 3 days. Once 21 days have elapsed following enrolment, the participant’s medical record will be reviewed to track any return ED visits, hospital admissions and additional healthcare contact. Admissions and ED visits reported by caregivers to study hospitals must be confirmed on medical record review. Similarly, at the six study hospitals where admissions and ED visits to non-study hospitals can be confirmed by administrative database review, non-study hospital ED visits and admissions reported on the survey will be confirmed. For study sites where visits and admissions to non-study hospitals cannot be confirmed by administrative database review, the caregiver’s report of and reason for these visits/admissions will be used to determine whether the participant met the study definition of admission. The final trial analysis will take place after every participant has reached 21 days after enrolment and all the data have been collected and cleaned. The analysis will be performed in a blinded manner.

The final trial analysis will use a Bayesian inferential framework based on the posterior probability that the EpiDex combination is superior to placebo for the primary and secondary outcomes. It will follow the intention-to-treat principle. The EpiDex combination will be declared superior to placebo if the posterior probability of superiority is above 99%, with simulations confirming a type 1 error rate of 4.1% with a probability of hospitalisation equal to 0.35 and a power of 81% with a target difference of 8%. Due to the likelihood principle, corrections for multiple comparisons will not be used. All estimates for the treatment effect will be reported using 95% high density posterior credible intervals, calculated using R [18] interfacing with Bayesian software such as JAGS, stan or INLA [19–21].

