### Handling of missing data

Participant medical record/database review will minimise the presence of missing data for many outcomes. Descriptive statistics on the proportion of missing data by treatment arm will be provided for the outcomes and the covariates. If the level of missingness is below 5%, we will undertake a complete case analysis. If greater than 5% of the data are missing, we will evaluate if there are any differences between the baseline characteristics for participants with and without missing data. Using this evidence, we will determine whether a complete case analysis is valid. If covariate outcomes are missing and a complete case analysis is not valid, the primary analysis will be a joint Bayesian analysis of the missingness mechanism and outcome model. In general, we will not jointly model or impute missing outcomes. If outcomes are missing and a complete case analysis is not used, then we will report descriptive statistics for this outcome and the reasons that individuals were lost to follow-up.

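### The primary model adjusts for site only and so forgoes precision that a short, prespecified set of baseline covariates could add

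*SAP article*

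**What the plan says.** Under Analysis for the primary endpoint, the probability that EpiDex lowers hospitalisation is obtained "using hierarchical Bayesian relative risk regression, adjusted for site". The prior for the treatment effect comes from expert elicitation. Site is also the only stratification factor: "Eligible participants will be randomised using permuted-block randomisation, stratified by site".

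Under Baseline characteristics, the SAP states: "We will also collect baseline clinical characteristics (respiratory distress assessment index (RDAI) [23], oxygen saturation, respiratory rate, heart rate, and temperature". Age, length of symptoms and previous episodes are collected as well. These data are summarised by arm, and the clinical importance of any imbalance is to be noted. No use of them in the primary model is described.

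Additional analyses lists a complete case analysis and a prior sensitivity analysis, but no covariate-adjusted one. The Heterogeneity of treatment effects analysis builds a risk model that ignores treatment. Its minimum list includes age, length of illness and previous wheezing, but neither RDAI nor oxygen saturation.

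The decision rule and its operating characteristics are under Statistical principals: "The EpiDex combination will be declared superior to placebo if the posterior probability of superiority is above 99" per cent. The simulated false-positive figure is given as "type 1 error rate of 4.1% with a probability of hospitalisation equal to 0.35". The design's sensitivity to a real effect is put at "a power of 81% with a target difference of 8" per cent.

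**The concern.** If baseline variables predict admission, conditioning on them removes outcome variance that otherwise stays in the comparison of arms. The interval becomes narrower, and the posterior probability is more likely to pass 99% when the treatment works. The SAP itself expects some baseline variables to predict outcome, since it forms ten risk strata from them. Yet it uses none of them where precision matters most.

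Timing matters too. If severity turns out to differ between arms, no adjusted analysis of the primary outcome is named in advance. Any adjustment made after seeing the imbalance would be post hoc.

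**Working it through.** **Inputs from the SAP.** 410 analysable per arm (Sample size calculation); hospitalisation probability 0.35, type I error 4.1%, target difference 8 points (Statistical principals).

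**Assumptions.** The 0.35 also applies to the placebo arm in the power statement, so the comparison is 0.35 versus 0.27. R² is the share of outcome variance that the covariates explain. The SAP gives no value, so a range is shown.

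**The plan's own figures.**
- Recruitment: 410/0.95 = 431.6, so 432 per arm and 864 in total. This reproduces.
- Power: with a flat prior, the 99% rule gives type I error of about 1.0% and power of about 56%. The stated 4.1% must therefore come from the informative prior, whose parameters the article does not print. Illustrative Beta priors calibrated to 4.1% gave 71% to 86% power, depending on how prior weight is split between arms. The stated 81% is attainable, and can be neither confirmed nor refuted.

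**Data-only baseline at one-sided 4.1%.**
- SE = √[(0.35×0.65 + 0.27×0.73)/410] = √(0.4246/410) = 0.03218.
- 95% width = 3.92 × 0.03218 = 0.126, or 12.6 points.
- Power = Φ(0.08/0.03218 − 1.739) = Φ(0.747) = 77.2%. A pooled SE gives 77.0%.

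**With adjustment.** The SE is multiplied by √(1 − R²).

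| Assumed R² | SE (points) | Power | Gain (points) | 95% width (points) |
|---|---|---|---|---|
| 0 | 3.22 | 77.2% | – | 12.6 |
| 0.01 | 3.20 | 77.6% | 0.4 | 12.6 |
| 0.05 | 3.14 | 79.1% | 1.9 | 12.3 |
| 0.10 | 3.05 | 81.1% | 3.9 | 12.0 |
| 0.20 | 2.88 | 85.1% | 7.9 | 11.3 |

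The scaling was checked by simulating a standardised risk difference with one normal severity score (2,500 trials per setting). Variance fell by 5%, 11%, 15% and 26% at R² of about 0.05, 0.10, 0.165 and 0.28.

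**Allowing for the prior.** The design aims for an average posterior width below 9 points. Take 9 as the posterior width and 12.6 as the data-only width, in a normal approximation. The data then supply (9/12.6)² = 0.51 of the posterior precision, and the prior the remaining 0.49.
- R² 0.10: width = 9/√(0.51/0.90 + 0.49) ≈ 8.76, a reduction of 2.7% (data-only: 5.1%).
- R² 0.20: width = 9/√(0.51/0.80 + 0.49) ≈ 8.48, a reduction of 5.8% (data-only: 10.6%).

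The prior roughly halves the gain in the reported interval.

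**Minimally informative prior.** For the planned prior sensitivity analysis, 1.739 is replaced by 2.326. Power is 56% at R² 0, Φ(2.620 − 2.326) = 62% at 0.10 and Φ(2.779 − 2.326) = 67% at 0.20. This is where adjustment helps most, because that analysis rests on the trial's data alone.

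**The case against.** The strongest reply is that nothing here is wrong. The model respects the stratification, is clearly specified, and gives a valid comparison. Nothing suggests that 81% power relied on further covariates. All of that stands: this is a point about efficiency, not an error or a contradiction.

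A reader might also infer that the severity measures are strong predictors, or that they are complete in every infant. The SAP says neither. It gives no prognostic strength, and it foresees incomplete covariates: "Descriptive statistics on the proportion of missing data by treatment arm will be provided for the outcomes and the covariates". At R² near 0.01 the gain is negligible.

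A reader might infer that chance imbalance would bias the result. It would not: the unadjusted interval already allows for it. At R² 0.10, a 1.96-SE imbalance in severity (1.96 × √(2/410) = 0.14 SD) shifts the difference by about 0.137 × √0.10 × √(0.31 × 0.69) = 0.020, or 2 points. That is random error which adjustment would reduce.

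The practical objections also have weight. A log-link model with continuous covariates can give fitted risks above 1. The prior was elicited on marginal arm probabilities, so how it enters an adjusted model must be stated. Subgroup models, the first-episode analysis and the risk strata take some account of prognosis, but none replaces adjustment of the primary estimate. These are modest pieces of analysis work. They reduce the size of the point but do not remove it.

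**Conclusion.** The point holds as a recommendation. The primary model forgoes precision available from baseline data that the trial plans to collect. The data-only gain runs from about half a power point to about 8 points over R² 0.01 to 0.20, and the gain in the reported interval is smaller once the elicited prior is included. These figures assume 0.35 versus 0.27, 410 per arm and a normal approximation. None of them is the trial's actual power, which depends on a prior that the article does not print. The SAP does not support the stronger conclusions that the trial is underpowered, that site-only analysis is invalid, or that the stated 81% is mistaken.

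**What to change.** Before data lock, which Trial status anticipates by the end of September 2025, amend Analysis for the primary endpoint to:

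- name a short covariate set in addition to site, for example age, RDAI, oxygen saturation and symptom duration, with the functional form of each;
- report the risk difference and relative risk standardised over all randomised infants in the analysis, so that the elicited prior still refers to marginal arm probabilities, and state how that prior enters the model;
- keep the site-only model as a named sensitivity analysis;
- give a fallback if the log-link model does not fit.

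Handling of missing data should say which models its covariate rule covers, and should keep infants with a missing baseline value in the analysis. This matters because complete case analysis is allowed below 5% missingness. Losing 5% of infants multiplies the variance by 1/0.95 = 1.053, which cancels the whole gain at R² 0.05 (0.95 × 1.053 = 1.00).

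The 4.1%/81% simulations should be repeated under the adjusted model. No new data are needed; the cost is a short SAP amendment and some simulation and programming time.
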